#### Radiotherapy-planning

In order to ensure accurate reproducibility of patient positioning, the patient is immobilized using a ProSTEP (ITV, Innsbruck, Austria). CT scans are obtained in the immobilization device in 3 mm-slices. Target volumes and organs at risk are defined using Siemens TPS Version, Syngo RT Planning VC13A for contouring and dose calculation. The target volume is defined according to the RTOG consensus guidelines [21]. A margin of 5 mm and 7 mm in beam direction will be used to create the PTV (planning target volume) according to internal standards. OARs are small and large bowel, sigma, posterior wall of the rectum, bladder and femoral heads. Tolerated maximum doses to OARs must not exceed the TD5/5 for each organ [22].

#### Radiation therapy

After validation of the treatment plan by the radiation oncologist and the physicist in charge, treatment is applied in daily fractions of 5–6 × 1.8 Gy per week to a total dose of 45–50.4 Gy using active raster scanning proton radiation. Total treatment duration hence is 4–5 weeks. Isocenter and patient positioning are checked daily by on-line orthogonal x-ray-imaging and by regularly performed off-line positioning control CT scans. Treatment time is expected to be about 35–45 min. Treatment will be carried out on an out-patient basis unless the patient’s condition requires hospital admission.

HDR-VBT-boost is applied the week after finishing percutaneous proton radiation to minimize the confounder of additional acute bladder and rectal toxicities. HDR-VBT-boost is delivered to the upper two thirds of the vagina by using a vaginal cylinder. Single fractions of 5 Gy to the vaginal mucosa at 5 mm depth are delivered (two fractions, cumulative dose 10 Gy), CT-based treatment planning is used for 3-D-optimization.

#### Monitoring during treatment/adverse events

Patients are evaluated weekly during radiotherapy. Radiotherapy-related toxicities are assessed using the National Cancer Institute (NCI) Common Toxicity Criteria (CTC) version 4.0. Toxicity will be evaluated pre-treatment, weekly during radiation therapy and at follow-up. Unacceptable toxicity for every individual patient is defined as unpredictable or irreversible ≥ grade 4 toxicity. Unacceptable toxicity resulting in premature termination of the whole trial is defined as any grade 5 toxicity, two consecutive grade 4 toxicities or 5 consecutive grade 3 toxicities.

Expectable possible acute toxicities (up to 3 months post radiation therapy) are fatigue, loss of appetite, weight loss, skin toxicity, nausea, vomiting, irritable bowel syndrome, diarrhea, proctitis, dysuria, hematological toxicity. All acute toxicities should resolve within a few weeks after radiation therapy. Late side effects are rare and are defined as symptoms appearing at least 3 months post radiation. These could include chronic diarrhea, malabsorptive syndrome, chronic bladder inflammation, enterocolitis, strictures, fibroses, ulcers, chronic bleeding. Very rare symptoms are fistulation, perforation, peritonitis, intestinal necrosis or ileus necessitating surgical intervention.

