## Methods/design

### Study design

The study is designed as a prospective single-center one-arm phase-II-trial evaluating the clinical feasibility and toxicity of postoperative pelvic radiation using proton therapy. Patients fulfilling the inclusion criteria will be treated with active raster scanning proton radiation up to total doses of 45.0–50.4 GyE in 1.8 GyE single dose fractions. 25 patients are planned to be enrolled in a time period of 2 years.

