### Study objectives

The primary objective of the trial is the assessment of safety and treatment tolerability defined as the lack of any CTC AE ≥ grade 3 gastrointestinal or urogenital toxicity or premature treatment abortion.

Secondary endpoints are clinical symptoms and toxicity according to the CTC AE version 4.0. criteria, quality of life assessed with the EORTC-QLQ30/−EN24/−CX24 questionnaires and progression-free survival.

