### Patient selection

Inclusion criteria according to the protocol are:Histologically confirmed cervical or endometrial cancerIndication for postoperative radiotherapyKarnofsky Index ≥70Age between 18 and 80 yearsWritten informed consent

Exclusion criteria are the following:patients refusal or incapability of informed consentimplanted active medical devices lacking approval for ion beam radiationmetallic implants in the radiation field, e.g. hip prosthesesprior pelvic irradiationparticipation in another clinical trial which might influence the results of the APROVE trial

Simultaneous chemotherapy is NOT an exclusion criterium.

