### Sample size calculation and statistical analysis

The APROVE trial is a prospective single-center one-arm phase-II-study. Primary endpoint is the evaluation of safety and treatment tolerability of pelvic radiation using proton beam radiotherapy. 25 patients will be included in the study. Sample size calculation was performed to demonstrate a treatment tolerability rate higher than 80% with a power of 1-β = 0.90 using a binomial test at a one-sided significance level of α = 0.1 under the assumption of an actual treatment tolerability rate of 0.96. The primary analysis includes all enrolled patients. In addition, a per-protocol analysis will be performed. For the primary endpoint, a point estimate for the tolerability rate will be calculated alongside a one-sided 90- and 95%- confidence interval. Methods of descriptive data analysis will be used to evaluate the secondary endpoints and safety data. This includes calculation of appropriate measures of the empirical distribution and graphical display of the results.

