### Duration of the study

The primary objective of the study is to prove good treatment tolerability of pelvic radiation using proton beam radiotherapy, defined as the non-occurrence of CTC grade 3 gastrointestinal or urogenital toxicities during radiotherapy and up to 3 months after its completion. To assess the primary endpoint, the final study visit will be 3 months after the last patient completed the radiotherapy. The study ends 2 years after the last patient was treated. Recruitment of the patients is planned over a time period of 2 years.

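### The grade 3 stopping limb counts consecutive toxicities without naming the unit; read as successive patients, it would rarely fire for scattered excess toxicity (3.6% of trials at a true 30%)

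*Protocol article*

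**What the plan says.** Under Monitoring during treatment/adverse events, the protocol article defines the toxicity that stops the whole trial as "any grade 5 toxicity, two consecutive grade 4 toxicities or 5 consecutive grade 3 toxicities". The sentence speaks of toxicities, not patients, and has no organ restriction, denominator or time window. The same section has toxicity graded before treatment, every week during radiotherapy and at follow-up, so one patient can contribute several records. It also sets a separate limit for the individual patient, at unpredictable or irreversible toxicity of grade 4 or worse. No other trial-level stopping rule is shown.

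The primary endpoint is narrower. Study objectives counts a patient as a failure for grade 3 or higher "gastrointestinal or urogenital toxicity or premature treatment abortion". Duration of the study places the toxicity part of this "during radiotherapy and up to 3 months after its completion". The section on sample size aims "to demonstrate a treatment tolerability rate higher than 80" per cent with 25 patients, "using a binomial test at a one-sided significance level of α = 0.1", "under the assumption of an actual treatment tolerability rate of 0.96". The planned failure rate is therefore 4%, and the rate to be excluded is 20%.

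**The concern.** A rule that ends a trial should give the same answer to everyone who applies it. This sentence allows at least three counts: five patients in a row, five events in a row, or five assessments in a row. If a running total was meant, *consecutive* is the wrong word.

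On the successive-patient reading there is also a problem of substance. One patient without grade 3 toxicity sets the count back to zero. A trial in which 10 of 25 patients have grade 3 toxicity would then usually pass this limb, because the rule responds to the order in which affected patients arrive and not to how many there are. Safety and tolerability are the primary objective of this single-arm trial, so a grade 3 limb that seldom responds to the overall rate gives little protection against the kind of toxicity the trial was set up to measure.

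**Working it through.** **Inputs.** From the protocol article: n = 25, tolerability to be exceeded 0.80, assumed tolerability 0.96, one-sided α = 0.1, power 0.90, and a grade 3 limb of five. Assumptions made here: patients are independent, each has one outcome, outcomes are taken in enrolment order, and all 25 are observed. Rates of 30%, 40% and 50% are illustrations and do not come from the protocol.

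**1. The plan's own figure.** With X the number of tolerating patients, X ~ Bin(25, π):
- P(X ≥ 23 | 0.80) = 0.0982, which is within 0.1
- P(X ≥ 22 | 0.80) = 0.2340, which is not
- P(X ≥ 23 | 0.96) = 0.9235

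The stated sample size reproduces. Success needs at least 23 of 25, so the primary test is lost at the third failure.

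**2. Five successive patients.** Let a(n) be the probability that a run of five has occurred by patient n, at a grade 3 rate p. Then a(n) = 0 for n < 5, a(5) = p⁵, and for n ≥ 6

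a(n) = a(n−1) + (1−p)·p⁵·[1 − a(n−6)].

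Setting the bracket to 1 gives an upper bound that can be checked by hand, p⁵ + 20(1−p)p⁵:
- p = 0.2: 0.00032 + 20 × 0.000256 = 0.00544 (exact 0.0054)
- p = 0.3: 0.00243 + 20 × 0.001701 = 0.03645 (exact 0.0361)
- p = 0.4: 0.01024 + 20 × 0.006144 = 0.13312 (exact 0.1283)

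A simulation of 400,000 trials per rate gave 0.0053 at 20% and 0.1286 at 40%.

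**3. Running total.** P(Y ≥ 5) = 1 − Σₖ₌₀⁴ C(25,k) pᵏ(1−p)²⁵⁻ᵏ. At p = 0.2 the five terms are 0.0038 + 0.0236 + 0.0708 + 0.1358 + 0.1867 = 0.4207, so P = 0.5793.

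| True rate | Five patients in a row | Five or more in total |
|---|---|---|
| 20% | 0.5% | 57.9% |
| 30% | 3.6% | 91.0% |
| 40% | 12.8% | 99.1% |
| 50% | 31.2% | 99.95% |

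**4. Order alone.** Fix the number of affected patients and let every ordering be equally likely. With 8 of 25 affected, 1.9% of orderings contain five in a row. With 10 of 25, 7.6% do.

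**5. Do the other limbs make up for it?** Whole rule in successive patients, no deaths, with an assumed share of the toxicity at grade 4. Ranges cover a grade 4 patient breaking or continuing a grade 3 run.

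| Grade 4 share | Total rate 20% | Total rate 40% |
|---|---|---|
| one tenth | 1.3–1.5% | 12–16% |
| one quarter | about 6% | 23–29% |
| one half | about 20% | 57–60% |

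The grade 4 limb helps materially only when much of the toxicity is grade 4.

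**6. Price of a cumulative count of five.** P(Y ≥ 5) is 0.0028 at 4%, 0.0980 at 10% and 0.3179 at 15%. The 4% also includes treatment abortion, so 0.0028 is an upper figure for toxicity alone. Five patients with gastrointestinal or urogenital toxicity in the primary window leave at most 25 − 5 = 20 tolerating, below the 23 required.

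**The case against.** The text never says patients. On an event or assessment reading, with weekly grading, the limb could fire much sooner; as a running total it works as in the right-hand column of the first table. The full protocol may define the unit, and a condensed article is not at fault for leaving detail to it. This stands as a limit: the low probabilities belong to one reading. The printed word nevertheless describes a run, and a run of patients is the natural sense.

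The contrast is largest at rates well above those the article reports: 4% planned failure, 0.7–8% complications needing treatment in the literature, and 1 of 11 patients (9%) with acute grade 3 gastrointestinal toxicity in a pencil-beam proton series. This limits the weight of the point. Stopping rules exist for rates nobody expected, so it does not remove it.

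A run can also signal a fault in planning or delivery, and a lenient grade 3 limb beside strict grade 4 and grade 5 limbs is defensible for acute effects expected to resolve within weeks. That is a reason to keep a run rule as well. It is not a reason to rely on one to detect a raised overall rate.

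Three stronger inferences are not supported:
- *That 20% is a stopping threshold in the plan.* It is the composite failure rate behind the primary test, limited to two organ systems plus abortion, while the stopping rule covers all toxicity.
- *That a cumulative rule would spare a calculable number of patients.* A pause need not be permanent, and these women have an indication for pelvic radiotherapy and would otherwise receive photons.
- *That the trial lacks safety stopping.* Any grade 5 event ends it, and the individual-patient limit applies throughout.

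**Conclusion.** The point holds conditionally. The unit of *consecutive* is not fixed. If it means successive patients, the grade 3 limb has about a 1 in 28 chance of firing at a true 30% rate (1/0.0361 ≈ 28) and 1 in 8 at 40% (1/0.1283 ≈ 8), where a total of five would fire in 91.0% and 99.1%. These figures rest on independent patients, one outcome each, and 25 observed in order, and they cover the grade 3 limb alone. The sample size, the primary test and its interpretation are unaffected. This is a weakness in safety monitoring that should be corrected while patients are being treated.

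**What to change.** Amend the stopping sentence under Monitoring during treatment/adverse events:

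- For gastrointestinal and urogenital toxicity in the primary-endpoint window, replace the run of five with a cumulative count. For example, five or more patients with grade 3 or higher radiotherapy-related toxicity trigger a pause in enrolment and a safety review.
- Keep the grade 5, grade 4 and grade 3 limbs for all other organ systems and for late toxicity, so that no current protection is lost. State the unit of *consecutive* there, and let runs that mix organ systems still count. Other organs matter because "Simultaneous chemotherapy is NOT an exclusion criterium", and haematological toxicity is on the article's list of expected effects; a cumulative count that included it would need a higher threshold, set by the clinicians.

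Five is an example, and the clinicians may choose another number. The cost is a short amendment and some unneeded pauses: about 0.3% of trials at the planned 4%, 9.8% at a true 10% and 31.8% at 15%. Since 23 of 25 tolerating patients are needed, no trial paused by this count could still have met its primary test, so the change costs no power.

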#### Follow up

Patients are included into standard gynecology follow-up program. Additionally, regular study visits at 6 weeks, 3 months, 6 months, 9 months, 12 months, 18 months and 24 months post treatment are intended. Each visit includes update of medical history, assessment of symptoms and treatment toxicity. In addition, pelvic MRI-scans are performed 3, 6, 9, 12, 18, 24 months post treatment and quality of life is assessed 6 weeks, 3, 6, 12 and 24 months post treatment (Fig. 1).

**Fig. 1 Fig1:**
[figure not shown]
Study schedule

### Duration of the study

The primary objective of the study is to prove good treatment tolerability of pelvic radiation using proton beam radiotherapy, defined as the non-occurrence of CTC grade 3 gastrointestinal or urogenital toxicities during radiotherapy and up to 3 months after its completion. To assess the primary endpoint, the final study visit will be 3 months after the last patient completed the radiotherapy. The study ends 2 years after the last patient was treated. Recruitment of the patients is planned over a time period of 2 years.

## Discussion

The prognosis for patients with cervical or endometrial cancer has improved dramatically over the last decades. This is mostly due to more intensive screening programs, better prevention but also improved therapeutic options. Thus, developing new therapeutic techniques in order to reduce therapy-associated long-term toxicities and to improve quality of life of cancer patients has become more and more important. With the development of IMRT the incidence of acute and chronic toxicities could already be reduced. Nevertheless, therapy-associated complications requiring medical treatment are a relevant issue: 7.7% of patients develop severe complications after 5 years with an increasing risk for complications of 0.3%/year [16]. The introduction of proton therapy into clinical practice over the last few years offers one more opportunity for better sparing of organs at risk. A recent study from Philadelphia could already show that also for gynecologic malignancies the use of pelvic proton therapy results in lower doses to OARs with simultaneously good coverage of the target volume [19]. This resulted in a low rate of therapy-associated side effects with only one patient developing acute gastrointestinal toxicity grade 3. This study consisted of only 11 patients. Further studies with bigger collectives are necessary to verify these finding and to evaluate long-term side effects and the impact on quality of life of patients treated with proton therapy for gynecologic malignancies.

## Abbreviations

cc: Cubic centimeters
CT: Computed tomography
DEGRO: German Society for Radio-oncology
ESGO: European Society of Gynaecological Oncology
ESMO: European Society for Medical Oncology
ESTRO: European SocieTy for Radiotherapy & Oncology
FIGO: International Federation of Gynecology and Obstetrics
GCP: Good Clinical Practice
GOG: Gynecologic Oncology Group
Gy: Gray
GyE: Gray-Equivalent
HDR: High Dose Rate
HPV: Human Papilloma Virus
IMPT: Intensity-modulated proton therapy
IMRT: Intensity-modulated radiation therapy
L: Lymphangiosis carcinomatosa
NCI CTC AE v4.0: National Cancer Institute Common Toxicity Criteria version 4.0
OAR: Organ at risk
PBS: Pencil beam Scanning
PORTEC: Post Operative Radiation Therapy in Endometrial Carcinoma
PSPT: Passive Scattering Proton Therapy
PTV: Planning Target Volume
RTOG: Radiation Therapy Oncology Group
TD: Tolerance Dose
VBT: Vaginal Brachytherapy
VMAT: Volumetric Arc Therapy
